### Secondary Outcomes

#### Dynamic muscle strength

Lower extremity peak strength was assessed using digital K400 Keiser pneumatic resistance machines (Keiser Sports Health Equipments, Inc., Fresno, CA). One repetition maximum (1RM) tests were performed according to de Vos and colleagues [37] unilaterally on knee extension, hip abduction and adduction; and bilaterally on knee flexion, leg press, and plantarflexion. Strength tests were performed twice at baseline approximately 1 week apart, and the higher of the 2 results was recorded as the 1RM. The mean (range) CV for the 9 exercises in this cohort was 13.1 (9.8–21.7) %.

#### Muscle Contraction Velocity

Peak muscle contraction velocity was assessed in a non-fatigued state on a separate day, several days after their final strength test. The test was performed at 20% baseline 1RM on Keiser resistance machines: unilateral knee extension, and bilateral knee flexion and leg press [37].

#### Muscle Endurance

Muscle endurance was assessed after resting from velocity testing. Participants were instructed to perform as many consecutive repetitions as possible at 90% of their baseline 1RM through their full range of motion in correct form. The test was terminated if correct technique was not achieved, a visible pause occurred, or the participant began experiencing significant pain in their knee joint. Number of repetitions, along with mean work, velocity and power were recorded for the first repetition and the last correct repetition. The ratio of last/first repetition power was used as an index of fatigue.

Muscle velocity and endurance were performed during the first training session, with loads based on the higher of the 1RM values obtained. Follow-up endurance testing was conducted using the same 90% 1RM load used during baseline testing.

#### Physical Performance

##### Walking Endurance

The 6-minute walk test, performed according to Guyatt and colleagues [38] was used to assess walking endurance to the nearest 0.1 m. The better of 2 trials 1 week apart was recorded. The CV in this cohort was 3.0 (0.0–13.0) %.

##### Balance

The Chattecx Dynamic Balance System (software version 4.20; Chattecx Corp, Chattanooga Group Inc., Hixson, TN) was used to assess balance. This system allows testing of static balance time and body sway via measurements from the force platform [39]. Three test conditions were performed with eyes open and with eyes closed in a random order and without prior practice: i) narrow bilateral stance on the platform sliding backward and forward at a speed of 8.3 s/cycle in the anterior-posterior direction; ii) narrow bilateral stance on the platform tilting up and down from 0 to ± 2 degrees in the anterior-posterior direction; and iii) unilateral stance of the preferred leg on still platform. Balance was tested for up to 30 seconds per test. A maximum of 3 trials was allowed to complete each test if participants lost their balance (touching hand rails, taking a step off the platform, requiring support from the assessor). If no attempt was successful, the trial with the longest time was recorded and only data from this trial was analyzed. Unilateral stance duration with eyes closed, summated maximum sway in 4 directions (medial, lateral, anterior and posterior), and number of trials needed to complete the 6 conditions were used as individual measures of balance performance.

Overall balance performance was examined using a balance index [40]. The balance index was calculated by summating all anterior-posterior and medio-lateral sway measures and time results respectively.

This index has been shown to be reliable and valid, and is sensitive to change over time with an exercise intervention in older adults [40].

##### Stair climb

Maximal stair climb was used as a proxy for lower extremity power [41]. Two trials were conducted of the 9-step stair climb with 30–60 seconds rest between each trial. The best of the 2 test results was used. Stair power was calculated according to the formula below [41,42]:

$$\text{Power (W)}=\frac{\text{Body Weight (N)}\;\times \text{Height of Stairs (m)}}{\text{Ascent Time }(\text{s})}$$

##### Chair stand

Five chair stand test, performed according to Guralnik and colleagues [43] was used as an index for lower extremity power/balance. Time taken, as well as number of stands completed was recorded. The need for assistance from armrests was also recorded (yes or no) and analyzed as a separate outcome.

### Gait Velocity

Gait analysis was performed using a 10-camera Motion Analysis system (Motion Analysis, Santa Rosa, California) set to sample at 100 Hz. Thirty-eight passive reflective markers were placed bilaterally on standard bony landmarks of the lower and upper body. Participants were asked to walk barefoot without any assistive devices at their self-selected normal and maximal speed for 5 trials. Gait velocity was defined as the mean horizontal velocity of the sacrum marker during 2 full strides and was averaged over 5 trials. The CV in this cohort of the 5 trials was 4.6 (0.7–12.5)%.

### Body Composition

Body mass index was calculated from fasting weight and stretched stature measurements [44]. Waist circumference was measured according to the International Diabetes Federation protocol [45]. Percent body fat and fat-free mass were estimated using bioelectrical impedance (BIA-101: RJL Systems, Detroit, MI) All participants were measured 3 times early in the morning after a 12-hour fast. The CV in this cohort for resistance was 0.03 (0.0–0.1)%. Fat mass and fat-free mass were calculated from the formula developed by Lukaski and colleagues for older adults [46].

### Questionnaires

All questionnaires were interviewer-administered in a private room using visual prompts.

Symptomatology and disability was assessed using the Western Ontario and McMaster Osteoarthritis Index (WOMAC) questionnaire [47]. Habitual physical activity levels were assessed using the Physical Activity Scale for the Elderly (PASE) questionnaire [48] and Harvard Alumni Questionnaire [49]. Depressive symptoms were assessed using the Geriatric Depression Scale (GDS) [50]. Physical self-efficacy was assessed for lifting objects, walking, jogging, climbing stairs, and doing push-ups using the Ewart Self-Efficacy scale [51]. Health-related quality of life was assessed using Version 2 of the Medical Outcome Survey 36-item Short-Form (SF-36) [52]. All questionnaires have been well validated in OA and elderly cohorts.

### Covariates

Covariates identified *a priori *included age, BMI, duration of OA, use of glucosamine and/or chondroitin sulfate, number of chronic diseases. Other covariates will be selected if potential confounders are identified amongst baseline participant characteristics.

### Definitions

Session compliance was defined as the number of sessions attended out of 78 available sessions (up to 1 month extension was given to make up any missed sessions during the 6-month intervention). Training intensity compliance was defined as the difference between the theoretical relative load and the actual relative load for exercise for each session. The theoretical relative load (relative to the most recent 1RM) and the actual relative load was calculated at 4, 8, 12, 16, 20, 24, and 26 weeks. The actual load was then subtracted from the theoretical relative load to get difference in relative loads. Difference should be equal to zero if training intensity compliance was perfect or the results will be negative if actual was greater than theoretical. A one sample t-test was then performed to see whether or not the difference in loads was significantly different than "zero", the ideal value.

Total tonnage per exercise was calculated by summating the training load by the number of repetitions completed for that exercise for the intervention (24 repetitions for 78 sessions (total of 1872 repetitions) per exercise for the PRT group and 16 repetitions for 78 sessions (total of 1248 repetitions) per exercise for the sham-exercise group).

Whole body total tonnage was calculated by summating the total summated loads of each exercises and multiplying that by the total number of repetitions of all exercises.

Dropouts were those participants who did not complete the intervention and did not complete their final assessment (i.e. loss to follow-up). Discontinued subjects were those who did not complete the intervention, but did complete their final assessment and were included in the complete case analysis.

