### Intervention

Participants randomized to the intervention group performed resistance training at 80% of their peak strength using pneumatic resistance machines (K400 model, Keiser Sports Health, Inc, Fresno, CA, USA). The exercises included unilateral knee extension, standing hip abduction and adduction; and bilateral knee flexion, leg press, and plantarflexion. All exercises were performed for 3 sets of 8 repetitions (6–9 sec/repetition) with 10–15 seconds rest between repetitions and 1–2 min rest between sets. Maximum strength tests (1 repetition maximum or 1RM) were performed fortnightly and a new 80% load was prescribed; in between strength tests participants were prescribed 3% increments in load per session as tolerated. An intensity rating of 15–18 on the Borg Rating of Perceived Exertion (RPE) scale [33] was considered optimal and was used to adjust the load between 1RM measurements to assure the intended continuous progressive overload. Exercises and or resistance were modified daily according to participants' symptoms. Full range of motion was utilized unless limited by pain. In some participants, severe pain throughout the range of motion required substitution of isometric exercises of particular exercises intermittently during the 6 month of training.

The sham intervention was designed to closely replicate virtually all of the elements of the active exercise condition (modality, setting, supervision, equipment, volume, duration, frequency) with the notable exception of intensity, as we hypothesized that intensity would be the critical prescriptive element leading to robust adaptations in both proximal (muscle and tendon strength/hypertrophy) and distal outcomes (cartilage morphology) outcomes.

Participants randomized to the sham-exercise group trained on the same equipment as the intervention group except hip adduction, and performed knee extension bilaterally. Minimal resistance was set on the machine (weight of bar/foot plates only) and no progression was introduced. Exercise volume was reduced to 2 sets of 8 repetitions, using same speed as in the PRT group.

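### A one-sample t-test of signed load differences against zero cannot show that the prescribed training intensity was delivered

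*Protocol article*

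**What the plan says.** In the protocol article, Methods, Definitions, the measure is introduced per session: "Training intensity compliance was defined as the difference between the theoretical relative load and the actual relative load for exercise for each session". The loads are then obtained at selected times only: "the actual relative load was calculated at 4, 8, 12, 16, 20, 24, and 26 weeks". The sign is kept: "The actual load was then subtracted from the theoretical relative load to get difference in relative loads". Its reading is given as: "Difference should be equal to zero if training intensity compliance was perfect or the results will be negative if actual was greater than theoretical". The one stated assessment is the test: "A one sample t-test was then performed to see whether or not the difference in loads was significantly different than" zero, which the article treats as the ideal. It gives no tolerance margin, no absolute deviation and no share of women or sessions on target. It does not say whether the test is run week by week, exercise by exercise or on pooled data.

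The Intervention section supplies the context. The target is 80% of peak strength. "Maximum strength tests (1 repetition maximum or 1RM) were performed fortnightly", after which a new 80% load was set. Between tests the load was to rise by 3% per session as tolerated. Perceived exertion was used to adjust it, and symptoms could change it from day to day. The same section names intensity as the element expected to drive the effect, and as the main feature that separates the active arm from the sham.

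**The concern.** The trial tests whether high-intensity loading slows cartilage loss. If the 6-month MRI comparison is null, a reader must be able to separate two explanations: the intended intensity does not work, or it was not delivered. Under-delivery is a real possibility, since the Adverse events section lists reduced intensity, limited range and a switch to isometric work among the deviations that occurred. Over-delivery relative to the target is possible too, through adjustment on perceived exertion.

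A significance test against zero answers a different question. Its null hypothesis is that the mean difference is zero, so failing to reject it is not evidence of agreement. Because the differences are signed, the mean can sit at zero while individual women are far off target. More erratic training widens the SD and makes a non-significant result more likely. The test therefore tends to look reassuring when delivery is poorly controlled and alarming when it is tightly controlled but slightly offset.

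**Working it through.** The article states no result, margin or power for this test, so there is no figure of its own to reproduce. The check is of how the stated test behaves.

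**Inputs from the article.** Signed difference d = theoretical minus actual relative load; null value 0; significance at 0.05 (Statistical analysis), taken here as two-sided because sidedness is not stated; target sample 63 with 20% dropout (Sample Size). That gives 63/2 = 31.5 per arm, so about 31, and 31.5 × 0.8 = 25.2, so about 25 after dropout.

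**Assumptions.** The article gives no SD or mean for d. I use SDs from 1.5 to 20 percentage points of 1RM and the means shown.

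**1. Cancellation.** Take 26 women, 13 at d = +15 and 13 at d = −15. The mean is 0. The SD is √(26 × 225/25) = 15.3 and the standard error is 15.3/√26 = 3.0, so t = 0/3.0 = 0 and p = 1.00. The mean absolute difference is 15 points, and no woman is within 5 points of target.

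**2. Zero mean with wide spread.** With d normal, mean 0 and SD 15, about 50% of women are more than 10 points off target. The test is non-significant 95% of the time.

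**3. A real shortfall missed.** Power comes from the noncentral t distribution with noncentrality √n × mean/SD.

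| True mean | SD | n = 25: noncentrality | n = 25: P(significant) | n = 31: P(significant) |
|---|---|---|---|---|
| 5 | 15 | 5 × 5/15 = 1.67 | 0.36 | 0.44 |
| 5 | 20 | 5 × 5/20 = 1.25 | 0.23 | 0.27 |

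A 5-point average shortfall would usually pass without a significant result.

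**4. A trivial shift flagged.** With true mean 1 and SD 1.5, the noncentrality at n = 25 is 5 × 1/1.5 = 3.33 and P(significant) is 0.89; at n = 31 it is 0.95. No woman would be materially off target, yet the test would nearly always reject.

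**5. Timing.** The definition refers to "the actual relative load for exercise for each session", but the calculation "was calculated at 4, 8, 12, 16, 20, 24, and 26 weeks". All seven are even weeks. If the fortnightly strength tests kept a regular two-week rhythm, every sampled week falls in the same half of the cycle, whichever week the tests occupied. The other half would then never be examined. The article does not say which weeks held the tests, which session of a sampled week was used, or whether missed sessions shifted the rhythm. This is a possibility, not an established bias.

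**6. Would an equivalence test serve?** The two one-sided tests procedure needs the 90% CI to lie within the margin. Its half-width at SD 15 is t(0.95, 24) × 15/√25 = 1.711 × 3 = 5.1 points at n = 25, and 4.6 points at n = 31. With 25 women and an illustrative margin of ±5 points, equivalence could not be shown even if the observed mean were exactly 0.

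**The case against.** The strongest reply has four parts.

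- **The decision rule is inferred.** The article calls a zero difference ideal and says it was tested. It nowhere says that a non-significant result will be reported as compliance. This is correct. A reader might infer that the plan declares perfect compliance whenever p exceeds 0.05, but the text does not go that far. What stands is that no other criterion is offered.
- **Other information exists.** The Statistical analysis section has data expressed as mean and SD or median and range, so a large SD around a zero mean would be visible. Tonnage is defined in the same section as compliance, and 1RM strength is a secondary outcome. These give partial information on delivery. None of them states how far individual sessions were from the prescription.
- **Detail may sit in a fuller document.** A margin or a table layout could well be left to one. The choice of test is not such an omission, because the article states it.
- **The consequence is small.** This is a process measure that gates no analysis. That is also right.

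Two further readings are tempting. A reader might multiply the time points by the exercises and see a multiplicity problem. The article does not say that separate tests were run, and the exercise count itself varies: six types are listed under Intervention, and nine exercises are counted under Dynamic muscle strength. A reader might also count the planned rise in load between strength tests as compliance error that the sampling misses. The measure is a difference from the theoretical load, so that rise cancels if the theoretical load includes the 3% steps. The article does not say whether it does.

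**Conclusion.** The concern holds as a weakness in how delivered intensity is judged. The stated test cannot show compliance. It gives t = 0 when an assumed 26 women are all 15 points off target in balanced directions. It detects a 5-point mean shortfall with probability only about 0.36 to 0.23 at n = 25 (SD 15 to 20), and it flags a uniform 1-point shift with probability about 0.89 (SD 1.5). All these means and SDs are assumptions, since the article reports none. The direction of the argument does not depend on them; the sizes do. The mismatch between a per-session definition and seven even-week calculations is on the page, but its effect is uncertain.

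The point is minor. A reader might infer that the primary result or the imputation is affected. The cartilage comparison does not use this measure. The compliance term in the imputation model is probably session attendance, because the Intervention section calculates compliance as the percentage of sessions attended. The weakness bears on how a null cartilage result can be interpreted.

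**What to change.** Drop the t-test as the criterion for intensity compliance. From the session records, report by arm and exercise:

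- the mean difference with its 95% CI;
- the mean absolute difference, which does not cancel;
- the share of sessions within a margin that the investigators fix before the tabulation is made.

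State whether the theoretical load includes the between-test increments, and use all sessions so that the definition and the calculation agree. If only the seven weeks can be used, say so in the definition and say where they fall relative to the strength tests. An equivalence test against the same margin is optional and may lack precision at this sample size, so the descriptive measures should carry the conclusion.

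The cost is more data entry and tabulation. No new participant data should be needed if loads were recorded at each supervised session, as the tonnage definition implies.

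### Whole-body tonnage is written as total load times total repetitions, so it exceeds the sum of the per-exercise tonnages by the number of exercises, which differs between arms (minor)

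*Protocol article*

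**What the plan says.** The Definitions section of the protocol article gives two tonnage rules in succession.

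- **Per exercise:** "Total tonnage per exercise was calculated by summating the training load by the number of repetitions completed for that exercise". The repetition total shown in parentheses for PRT is "24 repetitions for 78 sessions (total of 1872 repetitions) per exercise for the PRT group"; the sham counterpart is 16 a session, or 1248 in all.
- **Whole body:** "summating the total summated loads of each exercises and multiplying that by the total number of repetitions of all exercises".

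The Intervention section fixes how many exercises each arm performs. For PRT: "The exercises included unilateral knee extension, standing hip abduction and adduction; and bilateral knee flexion, leg press, and plantarflexion". Sham participants "trained on the same equipment as the intervention group except hip adduction, and performed knee extension bilaterally". The number of exercises therefore differs between the arms, and so does the split between one-limb and two-limb work.

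**The concern.** Tonnage is a sum of products: load times repetitions for each exercise, added over exercises. The per-exercise rule respects this, although it uses a word for adding where multiplying must be meant. The whole-body rule is a product of sums. It credits the leg-press load, for example, with repetitions performed on plantarflexion, knee flexion and every other machine.

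If the excess were the same in both arms, the PRT:sham ratio would survive and only the absolute values would be wrong. It is not the same, because the excess depends on the number of exercises and sham does fewer. The Intervention section presents sham as closely matched to PRT, with intensity as the notable exception. A reader would naturally use whole-body tonnage to judge how far apart the arms were in training dose. A rule that overstates both arms and exaggerates the ratio would mislead on that question.

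**Working it through.** **Inputs**

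- Sets and repetitions per session (Intervention): PRT 3 × 8, sham 2 × 8.
- Sessions (Definitions): 78.
- Named exercises (Intervention): PRT 6 (knee extension, hip abduction, hip adduction, knee flexion, leg press, plantarflexion); sham 5 (the same without hip adduction).
- Loads: not given in the article, so only ratios can be derived.

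**Step 1. Reproduce the article's repetition totals.**

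- PRT: 3 × 8 × 78 = 24 × 78 = 1872.
- Sham: 2 × 8 × 78 = 16 × 78 = 1248.

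Both agree with the article.

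**Step 2. Compare the two rules.** Let exercise *i* have load Lᵢ and repetitions Rᵢ, for K exercises.

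- Sum of per-exercise tonnages: T = Σ(Lᵢ × Rᵢ).
- Rule as written: W = (ΣLᵢ) × (ΣRᵢ).

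If every exercise has the same R, then T = R × ΣLᵢ and W = K × R × ΣLᵢ. Hence W/T = K, whatever the loads.

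Illustration with two invented loads, 100 and 20, at 1872 repetitions each:

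- T = 100 × 1872 + 20 × 1872 = 224,640.
- W = (100 + 20) × (1872 + 1872) = 449,280.
- W/T = 2 = K.

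**Step 3. Apply it to the two arms.**

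| Counting | PRT: W as a multiple of ΣL | Sham: W as a multiple of ΣL | Excess, PRT and sham | Inflation of PRT:sham ratio |
|---|---|---|---|---|
| By exercise name | 6 × 1872 = 11,232 | 5 × 1248 = 6,240 | 6-fold, 5-fold | 6/5 = 1.2 |
| By limb | 9 × 1872 = 16,848 | 6 × 1248 = 7,488 | 9-fold, 6-fold | 9/6 = 1.5 |

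The correct multiples of ΣL are 1872 and 1248. The limb count of 9 takes the three unilateral PRT exercises twice (3 × 2 + 3). The sham count of 6 is inferred: hip abduction twice, plus four bilateral exercises. The Dynamic muscle strength section does speak of a coefficient of variation, "The mean (range) CV for the 9 exercises in this cohort", but that concerns the strength tests and not tonnage.

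**Step 4. Other literal readings of the summed loads.**

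- If each load has already been summed over the 78 sessions (constant load assumed), the excess by name is 6 × 78 = 468 in PRT and 5 × 78 = 390 in sham. The ratio is still inflated 468/390 = 1.2 times.
- If the per-exercise tonnages are meant, repetitions enter twice. The excess is 11,232 and 6,240, and the ratio is inflated 11,232/6,240 = 1.8 times.

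Neither reading removes the error.

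**Step 5. Unequal repetitions.** The factor K is exact only when repetitions are equal. With invented loads of 100, 50, 40, 60, 200 and 150 and repetitions of 1872, 1500, 1400, 1800, 1872 and 1872, W = 600 × 10,316 = 6,189,600 and T = 1,081,400, so W/T = 5.7 instead of 6.

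**The case against.** The best defence is that the sentence is loosely worded and the calculation was right. The per-exercise sentence is already imprecise, and it uses a total of 1872 or 1248 for a count common to every exercise in an arm. If the repetition total in the whole-body rule means that common count, then (ΣL) × 1872 or (ΣL) × 1248 equals the sum of the per-exercise tonnages exactly under full attendance. This is possible, but the rule refers to the repetitions of all exercises taken together, so the words do not say it. What stands is that the article does not show that any tonnage value was actually computed wrongly.

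The defence also limits the consequences, and here it is right. Tonnage is not the primary outcome, a listed secondary outcome, an a priori covariate, a sample-size input or part of the Statistical analysis section. The compliance definitions do not use it. The arms are in any case separated by design, since sham used only the weight of the machine parts without progression.

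A reader might infer three stronger points that the article does not support:

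- **That a dose-response analysis is invalidated.** None is planned.
- **That the per-exercise totals wrongly assume full attendance.** The rule refers to repetitions completed, and 1872 and 1248 can be read as the full-attendance totals.
- **That isometric sessions must be excluded.** How to report substituted isometric work is a separate matter and does not follow from this arithmetic.

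**Conclusion.** The point holds as an inconsistency between two adjacent definitions, and it is minor. Followed literally, the whole-body rule overstates tonnage 6-fold in PRT and 5-fold in sham and inflates the PRT:sham ratio 1.2 times. This assumes one load per exercise, equal repetitions across exercises and counting by exercise name. The 1.5 figure is an upper case under a limb count that the article does not specify for tonnage, and should not be taken as established. It would also go too far to conclude that the trial's tonnage values are wrong: that depends on whether the written rule was the one applied, which only the trial team can confirm.

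**What to change.** Replace the whole-body sentence with a definition as the sum, over exercises, of the per-exercise tonnages, each being load times repetitions completed. State how unilateral exercises are counted and use the same convention in both arms. This matters particularly for knee extension, which is unilateral in PRT and bilateral in sham. In the per-exercise sentence, say multiplying where the text now says adding.

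The trial team should confirm which formula was used. If it was the sum of products, the cost is one corrected sentence. If it was the written rule, whole-body tonnage needs recalculating from the training logs before it is reported. No outcome analysis has to be rerun.
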